## 2.4 Statistical interim analyses and stopping guidance

The study did not have any pre-specified stopping rule for efficacy or safety.

## 2.5 Timing of outcome assessments

The primary and secondary outcomes will be recorded in e-CRF at the three follow-up visits: 30 days from hospital discharge ( $\pm 5$  days), 6 months ( $\pm 10$  days) and 12 months ( $\pm 20$  days) from randomization. Detailed information on the outcomes will be collected, including the date and time of outcome occurrence, at such visits.

Regarding the vaccine effects, all patients were evaluated for a period of 7 consecutive days after the vaccination date, by hospital interview or by phone, in order to evaluate and register local and systemic adverse events that may occur. The schedule of study procedures is given in the Table 1.

**Table 1 - Description of the procedures and visits of the VIP-ACS study**

|                                       | Hospital period | 30 days from Hospital discharge | 6th month of inclusion | 12th month of inclusion |
|---------------------------------------|-----------------|---------------------------------|------------------------|-------------------------|
| Assessments                           |                 |                                 |                        |                         |
| Screening/Randomization               | X               |                                 |                        |                         |
| Eligibility Criteria Review           | X               |                                 |                        |                         |
| Previous medical history              | X               |                                 |                        |                         |
| Socio-demographic data                | X               |                                 |                        |                         |
| Medications in use                    | X               | X                               |                        |                         |
| FICF                                  | X               |                                 |                        |                         |
| Clinical Events Evaluation     |                 | X                        | X               | X                |
| Physical Measures              |                 |                                 |                        |                         |
| Blood pressure, pulse, and vital data | X               |                                 |                        |                         |
| Physical examination                  | X               |                                 |                        |                         |
| Anthropometry                         | X               |                                 |                        |                         |

[figure not shown]

| Study Intervention                                   |   |   |  |  |
|------------------------------------------------------|---|---|--|--|
| Vaccination                                          | X | X |  |  |
| Evaluation of safety outcomes (7 days after vaccine) | X | X |  |  |

### 3. STATISTICAL PRINCIPLES

#### 3.1. Confidence intervals and P values

Significance testing will be 2-tailed using  $\alpha = 0.05$ , unless otherwise specified. All analyses and summaries will be produced using R software, version 4.0.3 (or higher), or SAS® version 9.4 (or higher). Confidence intervals, if applicable, were calculated at the 95% nominal confidence level (95% CI).

The primary efficacy outcome will be tested at 5% two-tailed significance level. The second outcomes family were tested following a fixed-sequence method [please, see section 5.4]. A fixed-sequence statistical strategy tests endpoint in a predefined order (see section 5.4), all at the same significance level alpha ( $\alpha = 0.05$ ). If an individual test during any step is not statistically significant, further treatment comparison may continue (i.e., reporting of p-values) but significance will not be claimed, and p-values were deemed as nominally significant.

#### 3.2. Adherence and protocol deviations

As this study does not contain administration of drugs, except the initial dose of vaccine, the extent of exposure does not apply. The adherence to study will be evaluated in terms of loss of follow-up, as presented in Section 4.4.

A protocol deviation is any noncompliance with the clinical study protocol, Good Clinical Practice, or Manual of Procedures requirements. The noncompliance may be on the part of the subject, the investigator, or study staff.

Major protocol deviations will be summarized by treatment group for all randomized patients. The categories of protocol deviations will include the following:

- Entered but did not satisfy enrollment criteria
- Received a disallowed concomitant treatment
- Received wrong treatment or incorrect dose

[figure not shown]

- Developed withdrawal criteria but not withdrawn
- Other (as appropriate)

Investigators may only implement a deviation from or a change to the protocol to eliminate an immediate hazard(s) to subjects.

The number (and percentage) of patients with major and minor protocol deviations will be summarized by treatment group with details of type of deviation provided. The patients that are included in the Intention to treat (ITT, see section 3.3) analysis data set will be used as the denominator to calculate the percentages. No formal statistical testing will be undertaken.

Due to the COVID-19 pandemic, some patients from the control group were expected to receive study vaccine out of their expected window according to the protocol. Constraints regarding transmission of COVID-19 among participants should they leave their homes to be vaccinated are a major reason for this concern. Therefore, there will be sensitivity analysis excluding patients from the control group who were not vaccinated within the protocol window of time (i.e.,  $30 \pm 5$  days after randomization).

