In this sense, and based on the results of the aforementioned meta-analysis, non-controllable factors (COVID-19) and the findings of the IAMI trial, we recalculated the VIP-ACS sample size using a statistical Win Ratio (WR) approach, for analysis of efficacy of the double-dose influenza vaccine compared to the standard dose vaccine, in which it was estimated that the inclusion of 1800 patients (900 per group) for a WR of 1.41 with a power of 82.6% and an alpha of 5 %. These data were obtained over 10,000 simulations, considering the following event rates in the control group: death, 7.0%; AMI, 3.4%; stroke, 1.0%; hospitalization for unstable angina, 2.7%; hospitalization for heart failure, 2.9%; emergency revascularization, 1.0% and hospitalization for respiratory infections, 1.0%, and assuming a reduction of these events with double-dose vaccine in: death by 2.0%; AMI by 0.9%; Stroke by 0.3%; Hospitalization for unstable

angina by 0.8%; Hospitalization for heart failure by 0.7%; Emergency coronary revascularization by 0.2% and Hospitalizations for respiratory infections by 0.3%.

Considering that the primary endpoint of the VIP-ACS comprises more individual endpoints than the IAMI trial, and from the meta-analysis studies, the sample size calculation proposed to the VIP-ACS to assess possible reductions in hierarchical events of the primary endpoint is comprehensive and conservative to the purpose of the study, and overcomes the external conditions involved in the COVID-19 pandemic.

The analysis of the primary endpoint will exclude hospitalizations for respiratory causes caused by COVID-19. To this end, a sensitivity analysis and other exploratory analysis of the impact of COVID-19 on VIP-ACS events are planned.

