### Expected absolute risk reductions for the components of the primary outcome (representing 28% relative risk reduction)

|                                                                  |      |
|------------------------------------------------------------------|------|
| Death                                                            | 2.0% |
| Myocardial Infarction                                            | 0.9% |
| Stroke                                                           | 0.3% |
| Unstable angina                                                  | 0.8% |
| Hospitalization for heart failure                                | 0.8% |
| Urgent revascularization                                         | 0.2% |
| Hospitalization for respiratory infection
(Excludes COVID-19) | 0.3% |

Sample size and power calculation were based on 10,000 simulations. Based on these aggregated data and assuming independence between events, Bernoulli distribution for event occurrence, exponential distribution of time to outcome, and a 28% relative risk reduction (RRR) with high dose group versus standard dose group, for a two-tailed  $\alpha = 0.05$ , we calculated that the study would have 82.6% power with 1800 patients enrolled (900 per group). This definition of RRR will be a conservative estimate based on a prior meta-analysis suggesting RRR of 48% with the influenza vaccination versus placebo among patients with ACSErro! Fonte de referência não encontrada. and similar to recent IAMI trial a MACE reduction in 28% in ACS patients using influenza vaccine. Of note, although in the IAMI trial the intervention group (in-hospital vaccination after ACS) was compared against placebo, most of the benefit occurred almost

[figure not shown]

immediately, with great separation of event curves within the first 45 days, when the incidence of cardiovascular outcomes is highest. Since we are also comparing the earliness of influenza vaccination, we also expect this magnitude of benefit to be reasonable in our study.

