### 3.3. Analysis populations

The following analysis populations will be defined for statistical analysis:

**Screened** – All patients screened for the study – having an acute coronary syndrome (ACS) during the hospitalization phase.

**Eligible but not randomized** – All screened patients who were eligible but not randomized due to the inclusion/exclusion criteria of the study.

**Intention to treat (ITT)** – All eligible patients who received a randomization number, and analyzed according to the group to which they were assigned, regardless of receiving the vaccine or not.

**Per Protocol (PP)** – All ITT patients who did not have major protocol violation. A protocol violation means a patient who was randomized but was not eligible (had not inclusion criteria or had at least one exclusion criterion); a patient who was treated with an immunization different from the one the patient was randomly assigned (e.g., intervention arm being

[figure not shown]

vaccinated after discharge). Patients vaccinated out of the window in the control arm due to the COVID-19 pandemic will still be included in the PP population, but a sensitivity analysis will be done excluding those patients as well (modified PP).

**Modified PP** –Due to the COVID-19 pandemic, some patients from the control group were not vaccinated within the expected study window or were vaccinated with a vaccine other than the study vaccination. Therefore, a modified PP population excluded these patients, as well as those ones that were not vaccinated at all (except for deaths occurred before vaccine could be administered)

**Safety** - All patients who received the vaccine. Patients who were vaccinated out of window or with vaccines other than study immunization (e.g., from an outpatient clinic) due to the COVID-19 pandemic were included in this analysis. Patients were analyzed according to the vaccination arm received, regardless of the randomized arm.

To avoid bias, if a patient had entered into study more than once, and in all these entries, this patient was considered eligible (i.e. met all inclusion/exclusion criteria), only the “first” enrollment will be maintained at the “Eligible patient population”, and the other(s) were excluded, due to duplicity.

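### SAP 3.2 and 3.3 treat control deaths before vaccination in conflicting ways: read literally, 3.2 builds in immortal time, and modified PP carries a selection bias of unknown sign

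*Combined protocol and SAP*

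**What the plan says.** **SAP 3.2.** Because of the pandemic, some controls were expected to be vaccinated outside their window, so "there will be sensitivity analysis excluding patients from the control group who were not vaccinated within the protocol window of time". The window is given there as 30 ± 5 days after randomization. No exception is made for death before the window, and the double-dose arm has no corresponding rule.

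**SAP 3.3.** Controls vaccinated out of window because of the pandemic stay in the PP population. A sensitivity analysis labelled modified PP then excludes them, together with controls given a non-study vaccine, "as well as those ones that were not vaccinated at all (except for deaths occurred before vaccine could be administered"). PP itself removes ineligible patients and those given an immunization other than the one assigned; its example is an intervention patient vaccinated after discharge. The end of the section makes ITT the primary efficacy population and PP and modified PP sensitivity populations.

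**SAP 2.3.** Death is first in the hierarchy, and pairs with a censored patient are compared only up to censoring. The section describes the first 45 days in an earlier trial as the period "when the incidence of cardiovascular outcomes is highest".

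**Visit anchor.** SAP 2.1 and 3.2, and protocol 3.5, count the control vaccination from randomization. SAP 2.5 reads "The primary and secondary outcomes will be recorded in e-CRF at the three follow-up visits: 30 days from hospital discharge", and SAP Table 1 heads its vaccination column the same way.

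**The concern.** Whether a control is vaccinated at day 25 to 35 becomes known only after randomization, and a control who dies earlier cannot meet the condition. If those deaths are dropped, the retained controls have a guaranteed survival period that the double-dose patients lack, at the top of the hierarchy. If the deaths are kept while surviving controls are dropped, early control deaths sit on a smaller denominator, and the result also depends on who missed the window.

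These analyses are meant to show whether the ITT result survives pandemic deviations. A distorted check could falsely contradict or falsely support it. A programmer following 3.2 would also build a different data set from one following 3.3.

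**Working it through.** **Inputs from the documents.** Control 12-month rates: death 7.0%, MI 3.4%, stroke 1.0%, unstable angina 2.7%, heart failure 2.9%, respiratory infection 1.0%, urgent revascularization 0.6% (SAP 2.3) or 1.0% (protocol 6.1). 900 per arm, two-sided 5% ("The primary efficacy outcome will be tested at 5% two-tailed significance level").

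**Assumed.** The share *f* of 12-month events before day 30, the share *q* of surviving controls who miss the window, and the late-event risk of those who miss relative to other surviving controls. At constant hazard, *f* for death is [1 − 0.93^(30/365)] / 0.07 = 0.00595 / 0.07 = 8.5%. Values of 25% and 40% represent front-loaded risk.

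**1. The plan's own figure.** Protocol 6.1 plans "for a WR of 1.41 with a power of 82.6"%, and SAP 2.3 states the same power. Simulating the SAP 2.3 model gives a median WR of 1.41 with SAP inputs and 1.39 with protocol inputs, so the WR reproduces. Power came out at 80.1% and 76.9%, not 82.6%. That is a separate matter and does not bear on this point.

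**2. Control death proportion by arithmetic, no true effect, neutral misses.** The double-dose arm stays at 7.0%.

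- Literal 3.2: 0.07(1 − *f*) / (1 − 0.07*f*). The share *q* cancels.
- Modified PP: [0.07*f* + (1 − *q*)·0.07(1 − *f*)] / [0.07*f* + (1 − *q*)(1 − 0.07*f*)].

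| *f* | Literal 3.2 | Modified PP, *q* = 30% |
|---|---|---|
| 8.5% | 0.06405/0.99405 = 6.4% | 0.05079/0.70179 = 7.2% |
| 25% | 0.0525/0.9825 = 5.3% | 0.05425/0.70525 = 7.7% |
| 40% | 0.042/0.972 = 4.3% | 0.0574/0.7084 = 8.1% |

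**3. Full hierarchical WR, no true effect** (above 1 favours double dose). Day 30 stands for the window and the double-dose arm is untrimmed. Expected WR is from 1.5 million patients per arm. Using 0.6% or 1.0% for revascularization makes no material difference.

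| *f* | Literal 3.2, neutral misses | Modified PP, neutral, *q* = 10–30% | Modified PP, neutral, *q* = 50% | Literal 3.2 / modified PP, *q* = 30%, misses at 2× late risk |
|---|---|---|---|---|
| 8.5% | 0.96 | 1.01 | 1.03 | 0.75 / 0.80 |
| 25% | 0.89 | 1.02–1.05 | 1.12 | 0.72 / 0.87 |
| 40% | 0.83 | 1.02–1.07 | 1.17 | 0.69 / 0.93 |

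For neutral misses, ITT and a day-30 landmark applied to both arms without conditioning on vaccination both give 1.00. A separate run with vaccination days spread uniformly over 25 to 35 gave 0.90 and 0.85 for literal 3.2 at *f* = 30% and 40%.

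**4. False-positive rates** (3,000 trials of 900 per arm, U-statistic variance, nominal 2.5% per side, *f* = 8.5 / 25 / 40%):

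- Literal 3.2, neutral misses, favours control: about 5 / 16–18 / 30–36%.
- Modified PP, neutral misses of 20–30%, favours double dose: 3.0–3.1 / 4.0–5.2 / 5.8–8.3%.
- Modified PP, 30% misses at 2× risk, favours control: 41 / 20 / 8%.

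**5. Sign of modified PP.** With 10 to 30% misses it falls below 1 once those who miss carry roughly 1.1 to 1.5 times the late risk. At half the risk it rises to 1.05–1.37 over misses of 10 to 50%.

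**The case against.** The strongest reply is that only one analysis is planned. SAP 3.3 labels the exclusion of out-of-window controls modified PP, names only PP and modified PP as efficacy sensitivity populations, and SAP 5.3 lists no further window analysis. SAP 3.2 introduces the exclusion by speaking of late vaccination, not death. On that reading the operative rule keeps early deaths and the immortal-time cohort is never formed. This is plausible, but 3.2 still states a different rule, and modified PP still selects surviving controls.

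A reader might infer that the two rules are biased in opposite directions by construction. That holds when misses are unrelated to prognosis. With sicker misses both favour control, and with healthier ones literal 3.2 can also exceed 1 (up to 1.27).

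A reader might also infer that both rules trim only the control arm. That is exact for 3.2. Modified PP inherits PP exclusions from both arms, trims by vaccine type, and names no arm for the never-vaccinated. The calculation leaves these other exclusions out.

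Nor is the exclusion window undefined: 3.2 anchors it to randomization. The discharge wording in 2.5 and Table 1 is a mismatch to reconcile.

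Finally, the larger distortions need front-loaded events. The plan's own sample-size model uses exponential times, and at constant hazard the neutral-miss figures are 0.96 and, with 10 to 30% misses, 1.01. That stands as a limit on size.

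**Conclusion.** The concern holds for the robustness analyses. The two passages conflict on control deaths before vaccination. Read literally, 3.2 gives an immortal-time bias against the double dose: null WR about 0.96 at constant hazard and about 0.83 to 0.90 with 25 to 40% of events before day 30, for prognosis-neutral misses. The immortal-time part is fixed by the rule; the net direction can still shift with the prognosis of those who miss. Modified PP carries a selection bias that is absent with no misses, small for neutral misses of 10 to 30% (1.01 to 1.07), and of unknown sign otherwise.

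The early-event share, miss rate and prognosis of those who miss are assumptions shown as ranges. The documents do not support inferring that the main result is compromised: ITT is primary, and the testing sequence in SAP 5.4 contains no PP test. This should be corrected, but it does not threaten the primary inference.

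**What to change.** State a single rule, worded identically in SAP 3.2 and 3.3, and do not select controls on having been vaccinated in the window. Either of these would serve:

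- **Censor at first deviation.** Follow all randomized patients from day 0, count death before vaccination as an event, and apply the same deviation rule to both arms. SAP 2.3 already compares pairs only until censoring. Unweighted, this assumes that deviators have the same later risk as the others. Inverse-probability-of-censoring weights are an optional refinement, but for a pairwise win ratio they need pair weights and predictors of deviation that the SAP does not yet specify.
- **Symmetric day-35 landmark.** Start both arms at day 35 among those still under follow-up, without conditioning on vaccination. Report it as answering only the post-landmark question, since it sets aside the early period.

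At a minimum, carry the death-before-vaccination exception into 3.2 and report modified PP as subject to selection bias of unknown direction.

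Reconcile the visit anchor as well: SAP 2.1 and 3.2 count from randomization, SAP 2.5 and Table 1 from hospital discharge.

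The cost is SAP wording, modest programming and somewhat wider intervals; weighting, if chosen, adds more.

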### 3.3. Analysis populations

The following analysis populations will be defined for statistical analysis:

**Screened** – All patients screened for the study – having an acute coronary syndrome (ACS) during the hospitalization phase.

**Eligible but not randomized** – All screened patients who were eligible but not randomized due to the inclusion/exclusion criteria of the study.

**Intention to treat (ITT)** – All eligible patients who received a randomization number, and analyzed according to the group to which they were assigned, regardless of receiving the vaccine or not.

**Per Protocol (PP)** – All ITT patients who did not have major protocol violation. A protocol violation means a patient who was randomized but was not eligible (had not inclusion criteria or had at least one exclusion criterion); a patient who was treated with an immunization different from the one the patient was randomly assigned (e.g., intervention arm being

[figure not shown]

vaccinated after discharge). Patients vaccinated out of the window in the control arm due to the COVID-19 pandemic will still be included in the PP population, but a sensitivity analysis will be done excluding those patients as well (modified PP).

**Modified PP** –Due to the COVID-19 pandemic, some patients from the control group were not vaccinated within the expected study window or were vaccinated with a vaccine other than the study vaccination. Therefore, a modified PP population excluded these patients, as well as those ones that were not vaccinated at all (except for deaths occurred before vaccine could be administered)

**Safety** - All patients who received the vaccine. Patients who were vaccinated out of window or with vaccines other than study immunization (e.g., from an outpatient clinic) due to the COVID-19 pandemic were included in this analysis. Patients were analyzed according to the vaccination arm received, regardless of the randomized arm.

To avoid bias, if a patient had entered into study more than once, and in all these entries, this patient was considered eligible (i.e. met all inclusion/exclusion criteria), only the “first” enrollment will be maintained at the “Eligible patient population”, and the other(s) were excluded, due to duplicity.

The primary efficacy analysis of the study comprises the ITT population. Safety analysis was made for the Safety population. Efficacy endpoints were performed in the PP and modified PP populations, and safety endpoints in the ITT population, as sensitivity analyses.

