### 3.5.1. Patient management in case of incorrect inclusion or randomization

In cases where the inclusion of the ACS patient is inadequate (for lack of criterion or diagnosis error or inversion of groups at randomization) or in case of error in the administration of the vaccine, the investigational HUB must contact the coordinating site that will evaluate the continuation, discontinuation or adequacy of the randomization of the patient involved. All the decisions made on this matter must be documented and described together with the patient's information in the CRF.

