## 4. TRIAL POPULATION

### 4.1. Screening data

The patient disposition tables will summarize the following:

1) For recruitment period and overall:

- The number of patients screened
- The number of patients who failed screening (non-eligible) - % calculated from the Screened population
- The number (%) of eligible patients into the study (% calculated from the Screened population) and the reasons for non-eligibility

2) For each randomization group and overall:

[figure not shown]

- The number (%) of randomized patients (ITT population) by site study
- The number (%) of randomized patients (ITT population) by site region and state
- The number (%) of patients in the different study populations (Eligible, Safety, ITT, PP and modified PP populations).
- The number (%) of patients who completed the study
- The number (%) of patients who withdrew from the study and associated reasons (% calculated from the Safety population)

The percentages will be calculated based on the number of randomized patients (ITT population), unless otherwise specified.

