### 4.3. Recruitment

A CONSORT flow diagram will be used to summarize the number of patients who were:

- Assessed for eligibility at screening
- Screened
- Ineligible at screening\*
- Eligible and randomized (ITT population)
- Eligible but not randomized\*
- Loss of follow-up\*
- Randomized and included in the primary analysis
- Randomized and excluded from the primary analysis\*

\*reasons will be provided.

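### The SAP's formal ITT definition admits only eligible randomized patients, while its other sections assume ITT is everyone randomized; read literally, it permits post-randomization exclusions from the primary analysis.

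*Combined protocol and SAP*

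**What the plan says.** SAP 3.3 defines ITT as "All eligible patients who received a randomization number, and analyzed according to the group to which they were assigned", whether or not they were vaccinated. The same section states that "The primary efficacy analysis of the study comprises the ITT population". The flow-diagram list in SAP 4.3 repeats the restriction ("Eligible and randomized (ITT population") and has a separate line, "Randomized and excluded from the primary analysis", for which reasons are to be given.

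Other parts of the SAP use ITT differently:

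- PP in SAP 3.3 is "All ITT patients who did not have major protocol violation", and the explanation that follows begins: "A protocol violation means a patient who was randomized but was not eligible".
- SAP 3.2 summarizes major deviations for everyone randomized, lists failure to meet the enrolment criteria as a category, and uses ITT as the denominator.
- SAP 4.1 says: "The percentages will be calculated based on the number of randomized patients (ITT population), unless otherwise specified".

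The protocol synopsis and Protocol 3.1 promise an intention-to-treat analysis with no eligibility condition. Protocol 3.4 makes allocation open to investigators, care team and patients. Protocol 3.5.1 refers wrongly included patients to the coordinating site, "that will evaluate the continuation, discontinuation or adequacy of the randomization of the patient involved".

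**The concern.** Intention-to-treat protects the comparison because membership is fixed at randomization. Adding eligibility to the definition makes membership depend on a judgement that can be made or revised later. In an open-label trial that judgement can be influenced by knowledge of the arm or of the patient's course, unless it is blinded or confined to baseline facts.

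Eligibility is also a live question here. Prior receipt of the same vaccine strains is an exclusion, and Protocol 6.1 says that most potential recruits during the pandemic had received them. SAP 4.2 limits this exclusion to the 12 months before inclusion and Protocol 3.2.2.2 gives no time limit, so a patient's status can depend on which document is applied.

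At stake is which patients enter the primary analysis. Two programmers working from this SAP could build different primary datasets, and each could point to a sentence in support.

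**Working it through.** The plan gives no figure to reproduce, so the check sets the definitions side by side. Let R be all randomized patients and E the eligible ones.

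| Place | What it implies for ITT |
|---|---|
| SAP 3.3, ITT definition | ITT = E and R |
| SAP 4.3, flow-diagram label | ITT = E and R |
| SAP 3.3, PP definition | ITT contains patients in R but not in E |
| SAP 3.2, deviation summary | Patients in R but not in E are counted over ITT |
| SAP 4.1, disposition tables | ITT = R |
| Protocol synopsis and 3.1 | Intention-to-treat, no qualifier |

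**Step 1: PP.** PP is ITT minus violators, and the first kind of violator named is in R but not in E. If ITT = E and R, nobody in ITT can be of that kind and the clause is empty. If ITT = R, it does what it says.

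**Step 2: deviations.** Under the literal definition, patients who failed the enrolment criteria would be in the numerator of a percentage but not in its denominator. Under ITT = R the percentage is coherent.

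**Step 3: ways out of ITT.** Vaccine receipt is irrelevant to ITT, so the stated ways for a randomized patient to leave it are ineligibility and the duplicate rule in SAP 3.3. That rule applies only when the patient was eligible at every entry, and it refers to an eligible population that the list in 3.3 does not define.

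**Step 4: safeguards.** Both eligibility reviews in the visit schedules (Protocol Table 2, SAP Table 1) are in the hospital phase. Neither document says that a later eligibility decision is blinded or limited to baseline information. The blind committee in the synopsis evaluates diagnostics and endpoints; no text asks it to decide ITT membership.

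**Step 5: scale.** Each 1% of patients removed is 0.01 × 1800 = 18 patients. The documents give no number of ineligible randomized patients, so any percentage is an assumption.

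For balanced removal unrelated to outcome there is no bias, only some loss of power. As an approximation, use the SAP 2.3 rates with its independence assumption:

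- Any-event proportion, control: 1 − (0.93 × 0.966 × 0.99 × 0.973 × 0.971 × 0.994 × 0.99) = 0.173.
- Any-event proportion, double dose: 1 − (0.95 × 0.975 × 0.993 × 0.981 × 0.979 × 0.996 × 0.993) = 0.126.
- A two-proportion test at two-sided 0.05 has 79.4% power with 900 per arm, and 78.6%, 77.4% and 75.1% with 882, 855 and 810 per arm (2%, 5% and 10% removed).

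The loss is 0.8, 2.0 and 4.3 points. This is not the win ratio calculation behind the SAP's 82.6%; it shows only how power falls as patients are removed.

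**The case against.** **The SAP mostly means all randomized.** Sections 3.2 and 4.1, the PP clause and the protocol all fit ITT = R, and the word eligible may mean only that the patient passed screening. This stands in part: the defect is an inconsistency, not an established exclusion rule. It does not remove the point, because the formal definition and the flow-diagram label say otherwise, and a formal definition normally governs.

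**Protocol 3.5.1 and the flow-diagram box prove little.** This largely stands. Section 3.5.1 concerns the management of wrongly included patients, requires decisions to be documented, does not mention analysis sets, and does not say whether those deciding know the allocation. The box is a reporting item that may be zero, and the duplicate rule gives it legitimate content. Neither shows an intention to exclude ineligible patients.

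**A stronger reading: a bias towards the double dose.** A reader might infer that ineligibility would surface mainly when controls attend for vaccination at about 30 days, so that surviving controls would be removed selectively. The documents do not support this. Visit V1 at 30 days is for both arms (Protocol 3.5), only the vaccination there is specific to controls, and no eligibility review is scheduled then.

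A worst-case figure can be made, but it does not follow from that account. With no true effect and any-event proportion 0.173 in both arms, suppose 5% of controls are removed and all are event-free for 12 months. The control proportion becomes 0.1731/0.95 = 0.1822. Pairs in which both have events split equally, so:

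- wins: 0.8269 × 0.1822 + 0.5 × 0.1731 × 0.1822 = 0.1664
- losses: 0.1731 × 0.8178 + 0.5 × 0.1731 × 0.1822 = 0.1573
- win ratio: 0.1664/0.1573 = 1.06

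Removing the same 5% from controls merely alive at day 30 gave a simulated win ratio of 1.00 with uniform event times, and 1.01 if half of all events fall in the first 30 days. The same worst-case removal from the double-dose arm would reverse the direction: 1/1.06 = 0.94.

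**Conclusion.** The point holds as an internal contradiction with a consequence for the primary analysis. SAP 3.3 and 4.3 restrict ITT to eligible randomized patients; the PP definition and sections 3.2 and 4.1 presuppose all randomized patients. Followed literally, the formal definition permits exclusion on eligibility grounds after randomization in an open-label trial, with no stated safeguard and contrary to the protocol's unqualified commitment.

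It does not go further than that. The documents do not show that any patient was excluded for this reason. The size and direction of any bias cannot be derived from them, since they depend on how many patients would be removed, from which arm, and how removal relates to outcome, none of which is given. It is worth correcting because the stated rule itself produces a set that is not intention-to-treat, and the correction is nearly free.

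**What to change.** - **SAP 3.3, ITT:** define it as all randomized patients, analysed in the arm assigned, whether or not they are later found ineligible and whether or not they were vaccinated. For a person randomized more than once, keep only the first randomization.
- **SAP 3.3, duplicate rule:** attach it to the ITT set in place of the undefined eligible population, and remove the condition that the patient was eligible at every entry.
- **SAP 4.3:** relabel the ITT line as all randomized patients. Keep the box for patients randomized but left out of the primary analysis, limit it to duplicate randomizations, and report the reasons.
- **SAP 3.3, PP:** leave ineligibility as a PP exclusion, where the SAP already places it. The PP clause and sections 3.2 and 4.1 then read correctly as they stand.

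The cost is a few lines of SAP text. The planned sample of 1800 does not change, no new data are needed, and any randomized patients who would have been set aside as ineligible return to the primary analysis.
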